## Abstract

**Background:**

Home haemodialysis (HHD), has shown improved clinical outcomes, as well as a better quality of life, compared to conventional in-centre haemodialysis (ICHD) but still has a global low prevalence among end-stage renal disease patients. Haemodialysis (HD) patients tend to be sedentary but only few studies, mainly in North American ICHD patients, have evaluated the level of activity in HD patients.

**Methods:**

SeCoIA is an observational, longitudinal, prospective, international, multicentric, study, conducted in metropolitan France and Belgium. The main objective of the study is to quantify the physical activity measured by the total daily number of steps, in HHD patients compared to ICHD patients. The SeCoIA study will include 80 HHD patients and 80 ICHD patients,. Secondary objectives will be to characterize the HHD population and to confirm HHD efficiency on clinical parameters, as well as quality of life (QoL), in current practice. Physical activity will be measured by a 3-axis accelerometer. Accelerometers have been shown to provide accurate information, on both physical activity and sedentary behaviour. Patients will be instructed to wear the device and complete a patient diary 7 consecutive days after inclusion and the first week of each month for 12 months. Decision to undergo HDD or ICHD is independent of the study and follow-up frequency remains at the discretion of the physician/centre. QoL and quality of sleep will be respectively assessed by the Kidney Disease Quality of Life 1.2 (KDQOL™) and the Pittsburg Sleep Quality index (PSQI) questionnaires at inclusion, 6- and 12-month visits. Patients presenting a restless leg syndrome (RLS) will also complete the International Restless Legs Syndrome rating scale (IRLS) questionnaire.

**Discussion:**

The SeCoIA study will be the first large cohort study (160 patients) evaluating physical activity, objectively measured with a 3-axis accelerometer, in HHD versus ICHD patients. The present study will also include a comparison of QoL with a focus on RLS between HHD and ICHD. It is anticipated that HHD patients will have an improved physical activity and QoL which should encourage physicians to further promote HHD.

**Trial registration:**

Clinical trial NCT03737578 study registered on November 9, 2018 (Retrospectively registered).

## Background

End-stage renal disease (ESRD) is a major concern of global public health. The Global Burden of Disease 2015 study estimated that, worldwide, in 2015, 1.2 million people died from ESRD, an increase of 32% since 2005 [1]. ESRD is a serious complication of many pathologies, such as diabetes, hypertension and the number of patients treated for ESRD keeps increasing [2]. ESRD is an important economic burden and is associated with a decrease in quality of life [2].

In France, according to the REIN report (French Network of Epidemiology and Information on Kidney Diseases), on December 31, 2016, 84,683 patients were receiving a renal replacement therapy, 46,872 (55%) were on dialysis and 37,811 (45%) were living with a functional renal transplant. Among dialysis patients, 93.7% received haemodialysis (HD) of which 54.6% in centres (ICHD) and only 0.8% at home (HHD) [3].

Even though several studies have shown an improved efficiency of dialysis, as well as a better quality of life in these patients, HHD prevalence remains low [4, 5]. FHN (Frequent Haemodialysis Network) [6] and FREEDOM (Following Rehabilitation, Economics and Everyday-Dialysis Outcome Measurements) [7] are the main studies that compared the effects of short-daily (ICDH and HHD) to conventional thrice-weekly ICHD, focusing on clinical and economic benefits. Both studies were conducted in the United States. In the FHN trial, frequent (6-times per week) ICHD, as compared to conventional (3-times per week) ICHD, was associated with significant benefits, in term of mortality and left ventricular mass [6]. FREEDOM, a prospective multicentre observational study investigating the benefits of daily (6-times per week) HHD, reports improved clinical parameters, as well as psychological state, in HHD versus ICHD patients. Among the clinical parameters, patients showed a decrease in restless legs syndrome (RLS), as well as a decrease in post-dialysis recovery time [8, 9].

Few data are available on physical activity, in HD patients and the rare studies are mostly small and performed in ICHD [10–14]. One study with 43 subjects (23 kidney transplant recipients and 20 ICHD patients) in Brazil, measuring physical activity with a multiaxial accelerometer, showed that ICHD patients tend to be more sedentary than kidney transplant recipient [13]. On the other hand, in the UK, one study with only 28 HHD patients showed no difference in physical activity, evaluated by 2 questionnaires, compared to healthy controls [12]. In the EXCITE (EXerCise Introduction To Enhance Performance in Dialysis) trial, a multicentric randomized controlled trial in Italian centres, poor physical performance predicted a high risk of mortality, cardiovascular events and hospitalizations in this population of 296 dialysis patients [15]. Furthermore, in a secondary analysis of EXCITE, a home-based exercise program showed improvement of physical performance of those patients [16].

To our knowledge, no study focuses on the physical activity of HHD compared to ICHD patients. SeCoIA (Self COnvective haemodialysis Investigation Analysis), is an, observational, longitudinal, prospective international, multicentric study, that will compare physical activity, measured with a connected 3-axis accelerometer, between HHD and ICHD. It has to be noted that the use of an accelerometer classifies the study as interventional in France. The other objectives of the study are to characterize HHD patients and to confirm, in current practice in France and in Belgium, the efficiency of HHD on clinical parameters, as well as quality of life.

## Methods

### Study design

SeCoIA is an observational, longitudinal, prospective, international, multicentric, cohort study comparing HHD patients to ICHD patients, conducted with metropolitan French and Belgian HD centres (Fig. 1).

**Fig. 1 Fig1:**
[figure not shown]
Flow chart of the SeCoIA study

Eligible HHD patients are adult patients, starting an HHD training or about to start an HHD. ICHD patients will be randomly selected (ratio 1:1) in each center among patients aged less than 80 years.

Decision to undergo HHD or ICHD is independent of the study. All included patients will be followed-up for 12 months or kidney graft or withdrawal of informed consent, which event occurred first.

### Objectives

The main objective of the SeCoIA study is to evaluate the physical activity in the daily life of patients in HHD (5 to 7 times a week) in comparison with 3 times a week ICHD patients.

Secondary objectives include: 1) comparison of physical activity in HHD patients on the days with HD or without HD; 2) description of the prescription procedures of the HHD; 3) comparison of blood pressure changes between the two HD modalities; 4) comparison of the frequency, duration and reasons of hospitalizations between the two HD modalities; 5) comparison of cardiovascular risk between the two HD modalities; 6) comparison of the quality of life of the patients between the two HD modalities; 7) evaluation of the quality of the sleep of the patients between the two HD modalities; 8) comparison of the percentage of patients with RLS and the severity of RLS between the two HD modalities; 9) comparison of the evolution of drug intake (iron, erythropoietin stimulating agents, phosphate-binding agents, vitamin D, calcium supplementation, calcimimetics, calcium carbonate, bicarbonates, potassium binders, oral anticoagulants, heparin, antihypertensives, lipid-lowering drugs, glucose lowering drugs, analgesics, drugs related to RLS and sleep disorders) between the two HD modalities; 10) evaluation of the number of subjects who stopped the HHD technique and causes of discontinuation; 11) comparison of characteristics (age, sex, body mass index and blood pressure) in patients wearing the 3-axis accelerometer or not.

### Study population

SeCoIA will include 160 male and female adult patients, 80 HHD patients and 80 ICHD patients.

#### Inclusion criteria

Male or female aged 18 years or over,Patient who dated and signed the consent form,Affiliation to Social Security System,

**Table Taba:** 

HHD patient	ICHD patient
Patient who begins or will begin HDD training (5, 6 or 7 times per week).	ICHD (3 times per week); incident or prevalent patient randomly selected within the same centre.

To avoid a great imbalance between the 2 groups, random selection of ICHD subjects will be restricted to patients aged less than 80 years old at the time of sampling.

### Study procedures

The investigator completes a paper case report form (CRF) at inclusion and at least once a quarter or during a monthly visit. The frequency depends on physician current practice.

At the end of the inclusion visit (V0), participants (except in case of explicit refusal) will receive a connected 3-axis accelerometer (FITBIT®Flex2™); 3-axis accelerometers have been shown to be accurate with a very low variability compared to other instruments [17] and can provide large amount of data on light-intensity physical activity and sedentary behaviour [18]. The patients will be instructed to wear the device on the arm opposite to arterio-venous fistula for 7-consecutive days (at least from awakening to bedtime), after inclusion and the first week of each month, and to complete a patient diary including start and end dates of 3-axis accelerometer use, days of HD and start and end body weight on the first day of HD of the same week. The device will be synchronized during all follow-up visits (V1-V12). Collected data will include the total number of steps per day, sedentary behaviour (minutes of light, moderate or high activity), sleep pattern (start and end time of sleep, minutes of sleep, number of waking-up).

The patient diary includes also questions on physical activity at inclusion and at the end of the study (adapted from [19]).

Quality of life (KDQOL 1.2 Kidney Disease Quality of Life) and quality of sleep PSQI (Pittsburg Sleep Quality index) questionnaires are to be filled, during a visit, by the patient, upon inclusion and then at 6 months and at 12 months or in case of premature withdrawal. For patients with a diagnosed restless leg syndrome (RLS) according to the investigator, the International RLS (IRLS) questionnaire will be filled at inclusion, 6 and 12 months or in case of premature withdrawal. If participant develop a RLS during the course of the study, the IRLS will also be completed at the visit with first report of RLS, and then 6 months and 12 months after inclusion.

When a Physidia device is used, some modalities of HD (duration of dialysis, blood pressure) may be collected from Physidia SAS.

### Study assessments

#### Primary outcome

The main criterion is the average number of total steps per day at 3, 6, 9 and 12 months.

^i^ Blood: hemoglobin, glycated hemoglobin, calcemia, phosphoremia, PTH, bicarbonates, alkaline phosphatase, ferritin, transferrin saturation, albumin, natremia, predialytic β2microglobulin; urinary assessment with the method of collection (sample, 12 h or 24 h urine): creatinuria, urea, proteinuria, microalbuminuriaEvolution of the blood pressure during the study period (V0-V12);Frequency and duration of hospitalizations during the study period (V0-V12);Cardiovascular complications;Quality of life of the patients estimated with questionnaire KDQOL-SF version 1.2 at inclusion, 6 and 12 months. KDQOL 1.2 questionnaire has been validated and is commonly used as a measure of quality of life in dialysis patients [20];Quality of the sleep of the patients through PSQI version 1.0 questionnaire evaluated at inclusion, 6 and 12 months. PSQI questionnaire assesses sleep quality over a one-month period [21];Drug intake during the study period (posology of drugs linked with ESRD);Percentage of premature withdrawal from the study and reasons;Percentage of patients with RLS during the study period and assessment of severity with an IRLS (International Restless Legs Syndrome rating scale) questionnaire [22].

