Daily HHD is associated with an increase in dialysis efficiency, as well as a better quality of life [4, 5], but still has a very low prevalence worldwide (2% in USA [31], 0.3% in Canada [32], 0.7% in France [3] 1–2% in the UK [33]), with the exception of Australia and New Zealand with a prevalence of respectively 9.6 and 22.8% [30, 34]. Large observational cohort studies generally report, at the clinical level, lower mortality and decreased hypertension and at the medico-economic level, decreased hospitalization duration [4]. A recent American study on more than 5000 chronic dialysis patients, analysed the quality of life depending on dialysis modality [5]. At baseline, home modality (HHD and peritoneal dialysis) patients had higher KDQOL scores than ICHD. Over time, patients who did not change dialysis modalities tended to maintain the same quality of life level. Furthermore, it was shown that patients switching from at-home to in-centre had a significant decrease of physical functioning over time but those patients may have been sicker with higher comorbidities [5]. The present study will allow to compare QoL between HHD and ICHD at inclusion and its evolution over a 12-month period.

RLS remains a debilitating burden for patients and is relatively common in HD population with a prevalence of 6–62% with a poor quality of sleep and a decrease in quality of life [7]. RLS has been associated with increased cardiovascular diseases [35] but not with increased mortality [36]. In the FREEDOM study, an intermediate report showed that over a 12-month period, short daily HD was associated with an improvement of RLS and quality of sleep [9]. A randomized controlled trial on subjects who presented a RLS showed that a conditioning program of aerobic and lower-body resistance 3-days per week for 12 weeks, improved the severity of symptoms [37]. The authors did not specify if HD subjects were included in their study but the HD population especially the HHD patients, could benefit from an exercise program. However, very little information is available, especially on the French HHD population [38]. In our study, one of the secondary outcomes of the SeCoIA trial is to estimate the frequency of RLS, to assess the severity of the symptoms and eventually to establish a link between RLS and physical activity, in the HHD population.

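### Read as written, the RLS percentage covers the whole of V0–V12, so resolution of RLS already present at inclusion cannot change it

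*Protocol article*

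**What the plan says.** The RLS outcome in the Protocol article, Secondary outcome measures, has two parts: "Percentage of patients with RLS during the study period and assessment of severity with an IRLS" questionnaire. The matching objective (Objectives, item 8) is "comparison of the percentage of patients with RLS and the severity of RLS between the two HD modalities", with no time point.

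In the same outcome list, blood pressure and hospitalizations carry the label V0–V12 for the study period. Quality of life and sleep quality are instead tied to inclusion, 6 and 12 months.

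The HHD entry criterion (table under Inclusion criteria) is "Patient who begins or will begin HDD training (5, 6 or 7 times per week").

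Under Study procedures, for patients with RLS diagnosed by the investigator, "the International RLS (IRLS) questionnaire will be filled at inclusion, 6 and 12 months or in case of premature withdrawal". For RLS that develops later, "the IRLS will also be completed at the visit with first report of RLS, and then 6 months and 12 months after inclusion". Table 1 lists the IRLS as completed where applicable.

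The Discussion cites an earlier 12-month study in which "short daily HD was associated with an improvement of RLS and quality of sleep", and describes RLS as "relatively common in HD population with a prevalence of 6–62" per cent.

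**The concern.** The prior evidence that the article cites is that RLS improves on short daily dialysis. For a yes/no status, improvement means that RLS present at the start is gone later. A percentage taken over a window that includes the start counts such a patient as a case, however early the RLS resolves. Because HHD patients are enrolled around the start of training, much of what is counted in that group arose before the exposure under study.

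The risk is that the two modalities are reported as having similar RLS frequency when RLS has resolved more often in one of them. The article names RLS as a focus in both the Abstract and the Discussion, so readers are likely to use this figure.

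**Working it through.** **Inputs.** The article gives no RLS rate, effect size or power; its sample size concerns steps per day only. The only RLS figure in it is the 6–62% prevalence range. The resolution and onset rates below, and equal prevalence at inclusion, are assumptions.

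**Formulas.** Let b be the proportion with RLS at inclusion, r the proportion of those whose RLS has resolved by 12 months, and i the proportion of the others with new RLS that is still present at 12 months.

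- Period percentage, V0–V12: b + (1 − b)i
- Percentage at 12 months: b(1 − r) + (1 − b)i

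The first expression has no r. If b and i are equal in the two groups, the period difference is zero whatever the resolution rates.

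**Case 1: equal onset.** b = 30%, i = 5% in both groups; r = 50% on HHD and 10% on ICHD.

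- Period, either group: 0.30 + 0.70 × 0.05 = 33.5%; difference 0
- 12 months, HHD: 0.30 × 0.50 + 0.70 × 0.05 = 18.5%
- 12 months, ICHD: 0.30 × 0.90 + 0.70 × 0.05 = 30.5%; difference 12.0 points

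The same r and i at the ends of the article's prevalence range:

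| b | Period, both groups | 12 months, HHD | 12 months, ICHD | Difference at 12 months |
|---|---|---|---|---|
| 6% | 10.7% | 7.7% | 10.1% | 2.4 points |
| 30% | 33.5% | 18.5% | 30.5% | 12.0 points |
| 62% | 63.9% | 32.9% | 57.7% | 24.8 points |

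**Case 2: fewer new cases on HHD.** b = 30%, r as before, i = 2% on HHD and 10% on ICHD.

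- Period: 0.30 + 0.70 × 0.02 = 31.4% against 0.30 + 0.70 × 0.10 = 37.0%; difference 5.6 points
- 12 months: 0.15 + 0.014 = 16.4% against 0.27 + 0.07 = 34.0%; difference 17.6 points

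The period percentage does respond here, but only to the onset part.

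**Case 3: unequal RLS at inclusion.** With equal i, the period difference is (b_HHD − b_ICHD)(1 − i). At i = 5%, each point of imbalance at inclusion carries through as 0.95 points, with no effect of modality.

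**IRLS part.** Suppose, for illustration, that half of the RLS patients score 8 and half score 24, and that the milder half resolves on HHD only. If resolved patients stop completing the IRLS, the mean is 24 on HHD against (8 + 24)/2 = 16 on ICHD, so the group that improved looks worse. If they go on completing it, this does not arise. The article does not say which applies.

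**Limit of a 12-month comparison.** For 18.5% against 30.5% with 80 per group, unadjusted, the pooled standard error is √(2 × 0.245 × 0.755/80) = 0.0680 and the unpooled one is 0.0673. Then z = (0.120 − 1.96 × 0.0680)/0.0673 = −0.20, which gives about 42% power. The 12-month measure can show resolution, but it would not be well powered under these rates.

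**The case against.** The strongest reply is that severity is half of this outcome. The IRLS is repeated at inclusion, 6 and 12 months, and objective 8 compares severity as well as percentage. This stands. A reader might infer that no improvement on HHD could appear anywhere in the RLS outcome, or that only new cases can move the percentage. The documents support neither. Falling IRLS scores may show improvement, and Case 3 shows that imbalance at inclusion also moves the percentage, which matters in a non-randomised comparison.

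A second reply is that the wording does not expressly say at any time during V0–V12. The blood pressure and drug items use the same window for repeated data, the RLS item lacks the V0–V12 label, and the analysis plan may report percentages by visit. That reading is possible. It is the less natural one, because the list names time points for quality of life and sleep and does not for the RLS percentage.

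A third reply is that the article states no hypothesis of RLS resolution; the Discussion speaks of estimating frequency and assessing severity. This also stands. The expected direction comes from the cited study, not from a stated hypothesis.

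A reader might also infer a bias from visit frequency, since "The frequency depends on physician current practice" and more visits give more chances to record RLS. The article requires at least quarterly recording for everyone and nowhere says that frequency differs by modality. This is a possibility, not a demonstrated bias.

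**Conclusion.** The point holds for the percentage part only. On its natural reading it is a V0–V12 period percentage, and resolution of RLS present at inclusion cannot change it. That follows from the definition and does not depend on the assumed rates. The size does depend on them: with 50% against 10% resolution and equal onset of 5%, the period measure shows no difference where a 12-month percentage shows 2.4 to 24.8 points across the article's own prevalence range, and 12.0 points at 30%.

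The IRLS is a partial safeguard. It is completed only in patients with diagnosed RLS, and the handling of resolved cases is not stated. The point is minor to moderate: it concerns one part of one secondary outcome and does not touch the primary comparison of steps.

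**What to change.** Define the percentage as RLS present at the 12-month visit, with 6 months as supportive, and compare the modalities with adjustment for RLS status at inclusion. Report separately the patients whose RLS resolved and those with new RLS. State how patients whose RLS has resolved enter the IRLS comparison; giving a score of 0 to everyone without RLS is one debatable option and is not needed for this correction. State also how patients who leave before 12 months are counted, given that questionnaires at premature withdrawal are already planned.

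The cost is a change of outcome wording, RLS status recorded as present or absent at the three questionnaire visits already scheduled, and a small amount of extra analysis. No new visit or procedure is needed.

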### Statistical methods

#### Sample size

We hypothesize a difference in the average number of steps of 1000 steps per day between HHD and ICHD patients with a standard deviation of 2178 steps [11, 13] identical in the 2 groups. With 5 repeated measures, a first autoregressive covariance variance matrix structure, an α risk of 5% and a power of 90%, the number of subjects depends on the correlation of the number of steps between 2 records for a given subject. No published data are available, also the sample size was calculated using different estimates of correlation from 0.4 to 0.6. Using a 0.6 correlation, 53 patients in each group are necessary. To take into account the number of non-evaluable subjects and to be able to adjust on confounding factors, the final sample is estimated to be 80 subjects in each group.

#### Statistical analysis

Standard descriptive statistics will be used to summarize the data in HHD and in ICHD patients. All results will be blinded to the study site. All statistical tests will be two-sided at the 0.05 significant level. No replacement of missing data will be done except for the main criterion of analysis where a missing quarterly value will be replaced by the last value available for that quarter [Last Observed Carried Forward (LOCF)]. If no data is available for a given quarter, no missing value will be replaced for that quarter.

The average number of steps per day at each recording will be used for the analysis of the main criterion. A repeated measurement analysis will be performed using generalized linear mixed model with adjustment on confounding factors at inclusion (age, sex, duration since start of HD, body mass index, diabetes mellitus, arterial hypertension and heart failure) as fixed effects and the intercept and the slope of time of recording as random effects. The covariance structure with the minimum Akaike information criterion (AIC) will be selected. Two-way interactions will be tested.

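### The primary step count fills a missing quarterly value from an earlier month of the same quarter, although monthly dated recordings could enter the planned mixed model at their own dates; the likely effect is small and the remedy nearly free

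*Protocol article*

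**What the plan says.** All of the following is in the protocol article.

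- **Study procedures.** The accelerometer is worn for seven days "after inclusion and the first week of each month". The patient diary logs when each wearing period began and ended, so the date of each recording should be known.
- **Primary outcome.** "The main criterion is the average number of total steps per day at 3, 6, 9 and 12 months".
- **Sample size.** The calculation uses five repeated measures with a first-order autoregressive structure. The assumed effect is put this way: "We hypothesize a difference in the average number of steps of 1000 steps per day between HHD and ICHD patients". Both groups are taken to have an SD of 2178. The result is 53 per group for a correlation of 0.6, raised to 80.
- **Statistical analysis, replacement rule.** "a missing quarterly value will be replaced by the last value available for that quarter". The limit follows at once: "If no data is available for a given quarter, no missing value will be replaced for that quarter".
- **Statistical analysis, model.** "The average number of steps per day at each recording will be used for the analysis of the main criterion". The mixed model has "the intercept and the slope of time of recording as random effects".

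**The concern.** The replacement rule and the model sit in the same section and do not fit well together. The model has a slope for the time of recording. The rule lets a month 1 or 2 recording stand in for month 3, and likewise in later quarters. If the filled value takes the quarterly time, a real measurement is entered at the wrong time. A likelihood-based mixed model needs no such fill, because it can use each recording at its own date and tolerates gaps under missing at random.

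The first quarter is the most exposed. Patients in the home haemodialysis (HHD) group enter when they start or are about to start training, while in-centre (ICHD) patients may be prevalent. A time trend is therefore more plausible in the HHD group, and an early value used for month 3 could displace the two groups differently.

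The article also leaves open which recordings enter the primary analysis. Primary outcome names four time points and Sample size uses five measures. Statistical analysis speaks both of a quarterly value and of each recording. If the recordings are quarterly, the intermediate months serve only to fill gaps. If they are monthly, the fill is redundant and would enter one observation twice.

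**Working it through.** **1. The plan's own figure.** Inputs from Sample size: difference 1000, SD 2178, five measures, autoregressive correlation 0.6, power 90%, 5% level (two-sided, from Statistical analysis).

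- One measure per patient, before rounding: 2 × [2178 × (1.960 + 1.2816) / 1000]² = 99.69.
- Variance factor for the mean of five measures: [5 + 2 × (4 × 0.6 + 3 × 0.36 + 2 × 0.216 + 0.1296)] / 25 = 0.5233.
- n = 99.69 × 0.5233 = 52.17, rounded up to 53. The stated figure is reproduced.
- With four measures the factor is 0.592 and n = 60. The stated figure therefore matches inclusion plus four quarters.

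**2. Displacement from the fill.** The article gives neither a trend nor a missingness rate, so both are assumed. Displacement = monthly change in the group difference × share of quarterly values filled × months early (1 or 2, taking the inclusion recording not to be a donor for the first quarter, which the rule does not say).

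| Change per month | Share filled | Displacement (steps) |
|---|---|---|
| 25 | 10% | 2.5 to 5 |
| 50 | 20% | 10 to 20 |
| 100 | 40% | 40 to 80 |

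The range is 2.5 to 80 steps, or 0.25% to 8% of 1000. A steeper assumed case lies inside it. If the difference grows linearly from zero and averages 1000 over months 3, 6, 9 and 12 (mean 7.5 months), the change is 1000 / 7.5 = 133 steps per month. With 20% of HHD values filled and no ICHD trend, the displacement is 0.20 × 133 to 0.20 × 267 = 27 to 53 steps, towards no difference.

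**3. Precision from using all recordings.** Assume the autoregressive correlation decays continuously, so 0.6 per quarter is 0.6^(1/3) = 0.843 per month. With generalised least squares weighting, as a mixed model applies, the variance factor is (1 + r) / [m − (m − 2)r].

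- Five quarterly: 1.6 / 3.2 = 0.500. Thirteen monthly: 1.843 / 3.722 = 0.495. Gain about 1%.
- Months 3, 6, 9, 12: 1.6 / 2.8 = 0.571. All of months 3 to 12: 1.843 / 3.253 = 0.567. Gain under 1%.

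Under constant correlation 0.6 the factor is (1 + 0.6(m − 1)) / m.

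- Five against thirteen: 0.680 against 0.631, a gain of 7%.
- Four against twelve: 0.700 against 0.633, a gain of 10%.

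**4. Simulation.** 53 per group, autoregressive 0.6 per quarter, true difference 1000 at 7.5 months, difference changing by 50 steps per month, 40% of recordings missing at random, 300 runs.

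| Analysis | Mean difference | SD of estimate |
|---|---|---|
| Monthly at true time | 998 | 316 |
| Quarterly with carry-forward | 980 | 317 |
| Quarterly, gaps left empty | 1008 | 349 |

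The simulation error of each mean is 18 to 20 steps, so these runs do not by themselves establish a bias. Carry-forward and monthly data are about equally precise, and both are better than quarterly data with gaps left empty.

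**5. Sample size after the change.** With least-squares weighting and autoregressive correlation, thirteen monthly and five quarterly recordings both need 50 per group. Under constant correlation, thirteen need 63 (99.69 × 0.631) and five need 68 (99.69 × 0.680). All are below 80.

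**The case against.** The strongest defence is that this is not ordinary last-observation-carried-forward. The rule uses the patient's own measured week from the same quarter and leaves an empty quarter empty, so it behaves like a visit window. A training-period value can affect only month 3, since later fills come from months 4–5, 7–8 and 10–11. Even at month 3 the point is conditional, because the article gives no training duration. This stands, and it is why the effect is small.

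Several stronger readings are tempting, and the document does not support them:

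- **That filled values are certainly mis-timed.** The article does not say which time a filled value takes. That coding commonly belongs in the statistical analysis plan, which is not shown.
- **That two thirds of the follow-up recordings are certainly discarded.** The quarterly reading is better supported by Primary outcome and Sample size, but "The average number of steps per day at each recording will be used for the analysis of the main criterion" can also mean every monthly recording.
- **That carry-forward brings bias and no gain.** Compared with quarterly data left unfilled it recovers precision (SD 317 against 349). It gains nothing only against monthly data at true dates (316).
- **That four time points against five measures is an error.** Inclusion plus four quarters makes five and reproduces 53 exactly. What stays open is whether the inclusion recording is an outcome or a baseline value.
- **That monthly data would sharpen the estimate by 5% even under the autoregressive assumption.** That figure (0.565 against 0.592, simple means) compares months 1 to 12 with months 3, 6, 9 and 12. It comes from averaging in months 1 and 2, and like for like the gain is about 1%.

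**Conclusion.** The point holds in a limited form. The article specifies a within-quarter fill that the planned model does not need, and it does not settle which recordings enter the primary analysis. Entering dated monthly recordings is the better method, and the wording under Statistical analysis has to be reconciled in any case.

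The likely consequence is modest: about 2.5 to 80 steps of a 1000-step difference. This rests on an assumed change of 25 to 100 steps per month in the group difference, 10% to 40% of values filled, and filled values taking the quarterly time. It would grow with a steeper trend, or if gaps were more frequent or differed between groups. The precision gain is about 1% under the plan's own correlation structure and reaches 7 to 10% only if the correlation is constant. Nothing here shows that the sample size is wrong or that the primary conclusion is in danger. The reason to act is that the better analysis costs almost nothing.

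**What to change.** In Statistical analysis, and correspondingly in the statistical analysis plan:

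1. Enter all monthly follow-up recordings in the mixed model at their actual dates, without carry-forward.
2. State whether the inclusion recording is an outcome or a baseline value, and align Primary outcome and Sample size with that choice.
3. Define the primary contrast as the adjusted group difference averaged over months 3, 6, 9 and 12, estimated from this model. This keeps the stated endpoint.
4. Keep the quarterly carry-forward analysis only as a sensitivity analysis, and state the time value that a filled observation takes.

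Do not simply delete the carry-forward rule while keeping quarterly data, because that loses precision. The cost is a few sentences and slightly more programming. No new data are needed, since the monthly recordings and dates are already collected, and 80 per group can stand.
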